## Abstract

**Background:**

Chronic scrotal pain is a common condition with a prevalence of 2.5–4.8% in male outpatients. Up to 40% of these patients report depressive symptoms and many feel isolated. Minimal invasive treatment is lacking, while spermatic cord injections of Botox® (BTX) have been proposed to offer long‐term pain relief.

**Study Design:**

This research protocol comprises a prospective multicentre, randomized, double‐blinded clinical trial drawing patients from other urological departments in the region of Southern Denmark.

**End Points:**

The primary end point will be reduction in pain evaluated by visual analogue score for pain at 3 months. Secondary end point will be length of effect of BTX injections along with changes in quality of life.

**Patients and Methods:**

The study will include 50 patients for randomization to either spermatic cord block with 100 IE BTX or sterile saline. All patients will prior to randomization undergo physical examination and will be asked to fulfil multiple questionnaires regarding pain and impact in daily life, that is, (1) visual analogue score for pain, (2) quality of life (EQ‐5D‐5L), (3) Chronic Prostatitis Symptom Index (NIH‐CPSI), (4) ICD‐10 depression questionnaire (MDI), (5) Likert global assessment scale, and (6) International Index of Erectile Function questionnaire. Physical examination and fulfilment of the questionnaires will be repeated multiple times throughout the study period of 12 weeks. After this time point, patients will be unblinded, and the control arm will be given the opportunity of cross‐over.

## BACKGROUND

1

Chronic scrotal pain (CSP) is a common condition with a prevalence of 2.5–4.8%.^1^ CSP covers a variety of problems causing discomfort or pain in the scrotum originating from the testis or other parts of the scrotum including ductus deferens and epididymis. CSP is defined as intermittent or constant unilateral or bilateral scrotal pain lasting for more than 3 months, with a significant impact on the patients' daily life.^2^ Up to 40% of these patients report depressive symptoms and many feel isolated.^3^, ^4^ The aetiology of CSP is not fully understood but can be related to surgical procedures such as vasectomy, inguinal hernia repair, scrotal surgery, and abdominal and groin surgery, even though no apparent cause can be identified in 25–50% of the cases.^5^, ^6^

When no obvious source of pain is found, the most common approach usually begins with conservative treatment including analgesia, antibiotics, and in some cases, anticonvulsants and antidepressants.^5^, ^6^, ^7^, ^8^ When conservative treatment fails, a minimal invasive procedure with local anaesthesia (LA) cord block is often used before more invasive treatments such as denervation, vasovasostomy, orchiectomy, or epididymectomy are considered.^8^ Spermatic cord block with LA has proven to significantly reduce pain in patients with CSP.^9^ However, the effect of an LA cord block has limited duration, and it has been proposed that a longer lasting effect could be obtained with the use of OnabotulinumtoxinA (BTX), because BTX is widely used in pain management in diseases such as chronic pain syndrome, myofascial syndrome, headaches, arthritis, and neuropathic pain.^10^, ^11^, ^12^, ^13^, ^14^, ^15^

BTX interferes with neural transmission in two ways: (i) a direct way by blocking the release of acetylcholine, the principal neurotransmitter at the neuromuscular junction, causing muscle paralysis. Function can be recovered by the sprouting of nerve terminals and formation of new synaptic contacts which usually takes 2 to 3 months.^16^, ^17^ (ii) An indirect way by preventing the release of neurotransmitters other than acetylcholine (e.g., substance P, somatostatin, and serotonin) which is involved in the sensitization and stimulation of peripheral nociceptors which would otherwise stimulate the central nervous system and cause the sensation of pain.^10^, ^18^

The experience with BTX in patients with CSP is still limited and is not an integrated part of the standard care. An open‐label study has been conducted by Khambati et al.,^19^ where BTX was injected into the spermatic cord in 18 CSP patients. They found a significant reduction in pain measured by visual analogue score for pain at follow‐up after 1 and 3 months. However, pain and tenderness returned to baseline after 6 months.^19^ Following this, they conducted a randomized study comparing LA cord block with LA + BTX cord block in 64 patients and did not find a significant difference between pain reductions in the two arms.^20^ Though the overall difference in pain reduction was not significant, differences in the effect and duration of the treatment between the patients were described in both studies. The differences need to be further investigated, and it is not known if specific subgroups of CSP patients, based on the aetiology of the pain, have different effects of BTX treatments. In addition to this, the effect of BTX alone has not been described for CSP patients in a randomized manner but only tested in combination with LA versus LA alone. The clinical potential and use of BTX injections in CSP patients is therefore not fully described and BTX is not used on a regularly basis in the standard care of CSP patients.

### Study design

1.1

This study is a randomized, placebo‐controlled, double‐blinded trial covering the Region of Southern Denmark. Patients diagnosed with CSP experiencing successful spermatic LA cord block can be included. See flow of participants in Figure 1.

**FIGURE 1 bco2349-fig-0001:**
[figure not shown]
Flow of participants. CSP, chronic scrotal pain.

The aim of this study is to fully investigate the effect of chemical denervation with BTX injections on CSP and elucidate whether the effect is different between CSP patients based on the aetiology of the pain. By performing a randomized study comparing BTX injections with placebo (saline) injections in CSP patients, the effect of BTX alone will be investigated for the CSP patient group and subgroup analysis will elucidate differences between patients.

### End points

1.2

Primary outcome is the success rate of BTX. According to the literature, an improvement of one point or more in pain, determined by VAS, when compared with baseline values will be considered a success.^19^, ^20^

Secondary outcomes are as follows:
Duration of the effect; andImprovement of quality of life based on questionnaires (EQ‐5D‐5L, NIH‐CPSI, MDI, L‐GAS, and IIEF).

### Eligibility criteria

1.3

Male subjects will be included in the study if he meets all the following inclusion criteria:
Age of 18–70 years;Unilateral or bilateral scrotal pain >3 months;No other identifiable pathology or cause of pain;Insufficient effect of conservative treatment with unreduced pain measured by VAS; andA positive effect of LA spermatic cord block with a reduction in VAS of minimum 1 point.

If any of the following criteria are met, the subject must not be included in the study:
Other pathological conditions in the scrotum, for example, varicocele, spermatocele, and epididymitis;Interest in trying to conceive with partner in the following 6 months;Local infection near the proposed injection site;History with an allergic reaction to BTX and/or human serum albumin;History of motor neuron disease or haemostatic disorder;Active urogenital cancer; andCurrent use of Botox injections which would result in a total dose of Botox higher than 300 IE in the span of 3 months.

## METHODS

2

### Intervention

2.1

After referral, patients will undergo a comprehensive workup including a thorough medical and psychological history and physical examination (i.e., inspection and palpation of penis, testis, funiculus, groin including inguinal channel, abdomen, digital rectal examination with evaluation of the prostate and pelvic floor muscles, hips, and column). In addition, investigations of lower urinary tract symptoms (i.e., uroflowmetry and bladder diary, furthermore urodynamics and cystoscopy if indicated), blood work (i.e., creatinine, haematocrit, white blood cells count, and C‐reactive protein, approximately 12 mL), and Doppler ultrasonography of the scrotum by an experienced radiologist to rule to examine for structural pathology and urine analysis (i.e., urine culture and test for chlamydia and gonorrhoea) will be included.

In case other pathological conditions are excluded, conservative treatment will be initiated with paracetamol 1000 mg four times a day, ibuprofen 400 mg three times a day, or alfuzosin 2.5 mg three times a day.^21^ If no pain relief occurs within 30 days, patients are offered funicle cord block with 10 mL lidocaine 20 mg/mL. In case of a significant decrease in scrotal pain measured by VAS, patients will be offered inclusion in the study if they fulfil the study eligibility criteria and provide written informed consent.

The patients will be informed at the consultation and given written information of
Presentation of the project;Patient information material including links to the pamphlets from The National Committees on Health Research Ethics: “Før du beslutter dig” and “Forsøgspersoners rettigheder i et sundhedsvidenskabeligt forskningsprojekt”;Contact information for the project leader; andQuestionnaires 1–6 as listed below.

Patients can consent to inclusion in the study at first consultation, but in case patients need time to consider participating, they will be given a proper amount of time and then contacted by phone. If they accept inclusion in the project, they will receive an electronic consent form by safe email (eBooks).

When patients accept inclusion in this study, they also accept retrieval of relevant information from patient records by the study manager, the sponsor, and representatives of the sponsor.

Standard information on age, sex, country of origin, length of symptoms, comorbidity, prior surgery, and medication used in the last 3 months will be collected from patient records.

Prior to BTX cord block, patients will answer the following questionnaires:
Visual analogue score for pain (VAS);Quality of life (EQ‐5D‐5L);Chronic Prostatitis Symptom Index (NIH‐CPSI);ICD‐10 depression questionnaire (MDI);Likert global assessment scale (L‐GAS); andInternational Index of Erectile Function questionnaire (IIEF).

For randomization, the research coordinator will place an information sheet containing the randomization in sealed envelopes (1:1 block randomization). At first treatment, the research coordinator will open a sealed envelope revealing the randomization and prepare the solution needed. The patient and physician will be blinded for the treatment.

In both groups, injection of either BTX or sterile saline will be given approximately 1–2 cm distal to the superficial inguinal ring near the spermatic cord using a gauge 23 needle. Before injecting the solution, the syringe is aspirated to exclude intravascular injection. The intervention arm will be given an injection of 50 IU BTX (Botox®, AbbVie A/S, Copenhagen) in a solution of 5 mL sterile saline both lateral and medial to the funicle for a total amount of 100 IU BTX mixed in 10 mL sterile saline. The control arm will receive two injections of a total of 10 mL sterile saline in the same manner. Both groups will be observed for 30 min after the injections. After 3 months at the end of the follow‐up, patients in the placebo arm will be offered BTX injections if wanted.

### Sample size determination

2.2

Given that the true success rate for BTX, regarding the primary end point, is at least 0.70, the placebo success rate among controls is 0.20. We will need to study 23 experimental patients and 23 control patients to be able to reject the null hypothesis that the failure rates for experimental and control subjects are equal with probability (power) 0.9. The type‐I error probability associated with this test of this null hypothesis is 0.05. Considering potential dropouts, we will include 25 patients per group.

### Methods of data collection

2.3

The questionnaires that were answered prior to BTX cord block will be sent by secure email to all included subjects after 1, 2, 3, 4, 8, and 12 weeks. Physical examination will be repeated after 4, 8, and 12 weeks. The data will be stored in an approved logged database at the Odense Patient data Explorative Network only accessible by professional staff involved in the project.

### Data analysis

2.4

Univariate analysis and multivariate analysis will be performed: *T*‐tests will be used to compare means between groups and chi‐squared tests to compare dichotomous variables, and to adjust for unequal distribution of parameters at baseline, multivariate regression models, linear models in case of an interval scaled outcome, and logistic regression in case of a dichotomous outcome will be performed.

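### Questionnaires are collected at six follow-up time points, but section 2.4 names only methods that take one value per man; a repeated-measures model would use the data better at little cost

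*Protocol article*

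**What the plan says.** Section 2.3 (Methods of data collection) of the protocol article says that the questionnaires "will be sent by secure email to all included subjects after 1, 2, 3, 4, 8, and 12 weeks". In-person contact is less frequent: "Physical examination will be repeated after 4, 8, and 12 weeks". So there are six emailed assessments, three of them at the time of an examination.

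Section 1.2 (End points) lists two secondary outcomes: duration of effect, and improvement on five instruments (EQ-5D-5L, NIH-CPSI, MDI, L-GAS and IIEF). The abstract's end-point paragraph gives a time for the primary outcome: "reduction in pain evaluated by visual analogue score for pain at 3 months".

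Section 2.4 (Data analysis) says that t-tests "will be used to compare means between groups", with chi-squared tests for binary outcomes. To adjust for baseline imbalance it adds regression: "linear models in case of an interval scaled outcome, and logistic regression in case of a dichotomous outcome will be performed". The article names no mixed model, generalised estimating equation or other method for repeated values.

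**The concern.** Section 2.3 creates longitudinal data, and section 2.4 then names methods that, in their ordinary form, use one value per man. Two things follow.

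- **Missed questionnaires.** Follow-up is by email, and section 4 lets any man withdraw at any time. If the analysis rests on one week, a man without that week's value leaves the comparison, although his other weeks say something about where he stood.
- **Time course.** The Discussion justifies the schedule by how quickly the toxin acts: muscle weakening within 2 weeks, and neuropathic pain relief after 4 and 8 weeks. Duration of effect is itself a secondary outcome. None of the named methods describes how the difference between arms changes over the weeks.

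At stake are the precision and completeness of the secondary score comparisons in a trial of about 23 to 25 men per arm.

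**Working it through.** **The plan's own figure.** The article gives no figure for this point. Its one related figure is 23 per arm, from section 2.2, which assumes that "the true success rate for BTX, regarding the primary end point, is at least 0.70", a placebo rate of 0.20, type I error 0.05 and power 0.90.

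- Two-sided, uncorrected: n = [1.960·√(2·0.45·0.55) + 1.282·√(0.7·0.3 + 0.2·0.8)]² / 0.50² = (1.379 + 0.780)² / 0.25 ≈ 18.6.
- With continuity correction: (18.6/4)·[1 + √(1 + 4/(18.6·0.5))]² ≈ 22.5, so 23.

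The figure reproduces. It concerns the binary primary outcome at one time point and is untouched by what follows.

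**Inputs for this point.** There are six follow-up time points (section 2.3), with examinations at weeks 4, 8 and 12 (section 2.3). The article plans 25 men enrolled and 23 needed per arm (section 2.2). It gives no correlation between time points. I assume one common value r for every pair, including baseline, with equal variances, and take r = 0.5 to 0.7.

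**Step 1: one time point with baseline adjustment.** Relative to an unadjusted single value (variance 1), the variance is 1 − r².

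- r = 0.5: 1 − 0.25 = 0.75
- r = 0.7: 1 − 0.49 = 0.51

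The regression in section 2.4 achieves this if it includes the baseline score. That section ties adjustment to baseline imbalance and does not name the score.

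**Step 2: average of weeks 4, 8 and 12 with baseline adjustment.** The variance is (1 + 2r)/3 − r².

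- r = 0.5: 0.667 − 0.25 = 0.417
- r = 0.7: 0.800 − 0.49 = 0.310

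**Step 3: ratio, adjusted average to adjusted single time point.** The expression simplifies to (1 + 3r) / [3(1 + r)].

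| r | Single, adjusted | Average of 3, adjusted | Variance ratio | Standard error ratio |
|---|---|---|---|---|
| 0.5 | 0.75 | 0.417 | 0.56 | 0.75 |
| 0.7 | 0.51 | 0.310 | 0.61 | 0.78 |

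Over a wider range the variance ratio is 1.9/3.9 = 0.49 at r = 0.3 and 3.7/5.7 = 0.65 at r = 0.9.

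**Step 4: the week-12 contrast.** With every week-12 value present, a repeated-measures model with arm-by-time terms and baseline gives nearly the same week-12 estimate as baseline-adjusted regression at week 12. The ratios in step 3 do not apply to it. Its gain depends on missed week-12 questionnaires, for which the article gives no rate. As a scale, the planned allowance is 25 − 23 = 2 men per arm. If just those men lacked week 12, the single-week variance would rise by 25/23 = 1.09. A repeated-measures model could recover part of that, and only from men with an earlier follow-up value.

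**The case against.** The strongest reply is that t-tests and linear regression are valid for a comparison at one time point, and that week 12 is the natural one. The primary outcome is at 3 months, section 2.1 ends follow-up there, and section 6.1 times publication from the 12-week follow-up. An article also commonly leaves the time point of a secondary outcome, the ranking of instruments, any multiplicity rule and the handling of missing questionnaires to the analysis plan. All of this stands, so those omissions are not part of this point.

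A reader might infer more than the article supports:

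- **Thirty tests.** Five instruments at six time points make 5 × 6 = 30 possible comparisons. No passage says that each will be tested. Week 12 alone gives five.
- **Pooled rows.** No passage says that six rows per man will enter an ordinary regression as if independent.
- **Most of the data is necessarily discarded.** A t-test or linear model on one summary per man, such as his mean over the weeks, fits section 2.4 and respects the correlation.
- **A large power loss against a t-test.** Comparing a visit average with an unadjusted t-test overlooks the planned regression. If that includes the baseline score, it already lowers the single-week variance to 0.75 to 0.51 (step 1).

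What survives is narrower: section 2.4 does name its methods, and a better one exists for the data that section 2.3 collects.

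**Conclusion.** The point holds as an inexpensive improvement to the secondary score analyses. It is not an error that threatens the trial. As named, the methods drop a man from a single-week comparison when he misses that week, and they leave the time course undescribed.

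The size of the gain depends on the contrast. For the average over weeks 4, 8 and 12, the variance is about 0.56 to 0.61 of a single time point's, with baseline adjustment in both. This rests on an assumed common correlation of 0.5 to 0.7 between all time points including baseline. For week 12 with complete data the gain is small; with incomplete follow-up it depends on how many men miss week 12, which the article does not give.

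A reader might infer that the primary result is weakened. It is not: the primary outcome is a responder comparison, which the chi-squared test and logistic regression in section 2.4 can serve.

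**What to change.** In section 2.4, before any unblinded data are seen, state that each questionnaire score, and VAS as a score, will be analysed with a mixed model for repeated measures.

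- **Terms:** arm, time point, arm-by-time point and the baseline value, with covariance within patient (unstructured, or a stated simpler form if it does not converge; six time points need 6·7/2 = 21 parameters).
- **Data:** all men with at least one follow-up value.
- **Stated contrast:** the arm difference at week 12.
- **Supporting estimate:** the arm difference averaged over weeks 4, 8 and 12.

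The primary responder comparison stays as it is. The arm-by-time estimates would show how the difference develops within 12 weeks, although they do not by themselves define duration of effect.

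The cost is revised wording and slightly more programming, with no new data, contacts or patients. There are two drawbacks. The average can hide a late loss of effect, which is why week 12 remains the stated contrast. The model also assumes that whether a value is missing depends only on what has been observed.

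### Covariate adjustment is tied to observed baseline imbalance, and baseline VAS is not fixed as a covariate: a modest, free improvement, mainly for VAS analysed as a continuous outcome

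*Protocol article*

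**What the plan says.** The analysis plan is section 2.4 (Data analysis) of the protocol article. It opens with "Univariate analysis and multivariate analysis will be performed", names t-tests for means and chi-squared tests for dichotomous variables, and then gives the role of regression: "to adjust for unequal distribution of parameters at baseline, multivariate regression models, linear models in case of an interval scaled outcome", while "logistic regression in case of a dichotomous outcome will be performed". It names no covariate, does not say how inequality is to be judged, and does not rank the unadjusted and adjusted results.

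Baseline VAS is available for every patient: section 2.1 (Intervention) lists it first among the questionnaires completed before the cord block. It also enters the endpoint, since section 1.2 (End points) says that "an improvement of one point or more in pain, determined by VAS, when compared with baseline values will be considered a success". The abstract describes the endpoint differently: "The primary end point will be reduction in pain evaluated by visual analogue score for pain at 3 months". Section 2.2 sizes the trial on the binary version, assuming that "the true success rate for BTX, regarding the primary end point, is at least 0.70" and that the placebo rate is 0.20.

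**The concern.** Under 1:1 block randomisation, any baseline difference between arms is chance. Whether a covariate is worth adjusting for depends on how well it predicts the outcome, not on whether it happens to differ between arms. A rule based on imbalance therefore has two weaknesses. It can leave out the covariate most likely to be prognostic, baseline VAS, whenever the arms look alike on it. It also makes the covariate set depend on the data, in a trial of 25 patients per arm where sizeable chance differences are common.

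An article may leave the covariate list to a statistical analysis plan, so silence alone would be no finding. Here, though, a basis for adjustment is stated, and an analysis plan that followed it faithfully would inherit the weakness. At stake are precision for VAS as a continuous outcome and, if the reporting choice stays open, control of type I error.

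**Working it through.** **Inputs from the article.** Success rates 0.70 and 0.20, alpha 0.05, power 0.90, 23 evaluable patients per arm (section 2.2).

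**Assumptions.** The correlation r between baseline and week-12 VAS is not given; I take 0.5, with range 0.3 to 0.7, and equal variances at the two times. The power comparisons in step 3 use an illustrative effect of 0.8 SD, which is also not in the article.

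**1. The plan's own figure.** The two-sided, pooled, uncorrected formula gives

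n = [1.960·√(2·0.45·0.55) + 1.282·√(0.21 + 0.16)]² / 0.50² = 18.6.

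With the continuity correction, n = (18.6/4)·[1 + √(1 + 4/(18.6·0.50))]² = 22.5, so 23 per arm. The stated size is reproduced. It corresponds to an unadjusted comparison of two proportions, like the planned chi-squared test.

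**2. Variance of the treatment effect on continuous VAS.** With baseline VAS always in the linear model, the ratio is 1 − r² against a t-test on week-12 scores and (1 − r²)/[2(1 − r)] = (1 + r)/2 against a t-test on change.

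| r | versus week-12 scores | versus change |
|---|---|---|
| 0.3 | 0.91 | 0.65 |
| 0.5 | 0.75 | 0.75 |
| 0.7 | 0.51 | 0.85 |

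**3. What an imbalance trigger recovers.** Simulation, 23 per arm, 20,000 runs per setting. The trigger adjusts for baseline VAS only if its baseline t-test has p < 0.05, which happens in about 5% of trials; otherwise the week-12 t-test is used.

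| r | Power, unadjusted | Power, triggered | Power, always adjusted |
|---|---|---|---|
| 0.3 | 0.757 | 0.759 | 0.785 |
| 0.5 | 0.760 | 0.767 | 0.862 |
| 0.7 | 0.752 | 0.771 | 0.956 |

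The trigger does rather better on the spread of the estimate, because it acts on the worst imbalances. At r = 0.5 under no effect, the SDs of the estimate are 0.295, 0.286 and 0.258. The variance ratios to unadjusted are (0.286/0.295)² = 0.94 for triggered and (0.258/0.295)² = 0.76 for always adjusted. That is about a quarter of the available reduction, with little of it reaching power.

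**4. Effect implied by the design rates.** If change in VAS is normal with equal SD in both arms, 0.70 versus 0.20 implies a difference of 0.524 + 0.842 = 1.37 SD of change. A t-test on change at 23 per arm then already has power 0.995. A t-test on week-12 scores has 0.9997, 0.995 and 0.94 at r = 0.3, 0.5 and 0.7.

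**5. Responder endpoint.** Simulation, 23 per arm, 4,000 runs per setting, ranges over r = 0.3 to 0.7.

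| Rates | Chi-squared | Triggered | Logistic with baseline VAS |
|---|---|---|---|
| 0.70 vs 0.20 | 0.95–0.96 | 0.95–0.96 | 0.96–0.98 |
| 0.55 vs 0.20 | 0.70–0.72 | 0.70–0.72 | 0.76–0.81 |

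The adjusted likelihood-ratio test had type I error 0.062 to 0.066, so part of its apparent gain is not real. Expected successes at the design rates are 0.70·23 + 0.20·23 = 20.7, which leaves room for only a very short covariate list.

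**6. Type I error.** For continuous VAS, a trigger fixed in advance gives 0.050, 0.046 and 0.036 at r = 0.3, 0.5 and 0.7: no inflation. Reporting the smaller of the unadjusted and baseline-adjusted p-values gives 0.066, 0.074 and 0.082. The same choice on the responder endpoint gives 0.072 to 0.083. Each uses one candidate covariate.

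**The case against.** The strongest reply is that section 2.4 contains no explicit trigger. It says that both kinds of analysis will be performed, and the imbalance phrase can be read as a motive for adjusting, not a condition. There is no significance screen in the text. This stands in part: the models may always be run. Their covariates would still be chosen, on the stated purpose, by what looks unequal.

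Second, a reader might infer that the trial loses worthwhile power on its primary comparison. The document does not support that. Section 1.2 makes the outcome binary and section 2.2 sizes it at 0.70 versus 0.20, where the unadjusted test already has power of about 0.95. The gains of roughly ten points appear only at effects well below the 1.37 SD that the design rates imply.

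Third, a reader might infer that the plan inflates type I error. A trigger fixed in advance does not. Inflation needs a choice between results after they are seen, and nothing in the article plans such a choice; it only fails to exclude it.

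Fourth, baseline is not ignored altogether, since success is defined as change from it. That is correct, but subtracting baseline is less efficient than including it in the model across the whole assumed range of r.

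Finally, the unadjusted chi-squared test is valid after randomisation and matches the sample size calculation. Nothing here requires that it be demoted.

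**Conclusion.** The point holds in a limited form. The stated basis for adjustment is a poor one, and a fixed model with baseline VAS is better at no cost in data. For VAS as a continuous outcome the variance falls by 25% at r = 0.5. Over r = 0.3 to 0.7 the fall is 9% to 49% against week-12 scores and 35% to 15% against change. These figures rest on the assumed correlation. A trigger based on a significant baseline difference captures almost none of the resulting power.

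For the responder endpoint at the planned rates the gain is one to two percentage points, partly an artefact of a slightly liberal test; it would matter more only if the true effect were smaller than planned. The risk to type I error is conditional on a choice made after the results are seen. The sample size of 23 evaluable patients per arm is unaffected. This is an improvement that should be made, not a flaw that undermines the trial.

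**What to change.** 1. Delete the imbalance phrase from section 2.4 and name the covariates in advance.
2. For VAS as a continuous outcome, use a linear model that always contains arm and baseline VAS. For the secondary questionnaire outcomes, use arm and that questionnaire's own baseline score.
3. For the responder endpoint, fit the logistic model with arm and baseline VAS only, and check its type I error at this sample size before relying on it.
4. State in advance which responder analysis is primary. Keeping the unadjusted chi-squared test as primary preserves the match with the 23-per-arm calculation; making the adjusted model primary gains a little power but needs the small-sample check. Either is acceptable if fixed before unblinding.
5. Reconcile the abstract with section 1.2 on whether the primary endpoint is pain reduction as a continuous measure or a binary success, since that decides which model applies.

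The cost is wording in the protocol or analysis plan. The baseline values are already collected and no extra patients are needed.
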